**Figure 5. F5:**
[figure not shown]
Saved contact and invitation to the participant for the intervention phase. (A) The contact is saved as “Intervention PDM 1” as this is the contact for participant 1 from the intervention group who is hypertensive (physician diagnosed and taking medication). (B) Chat page of participant 1. Translation of the message: “Welcome to this phase of the study. In this phase, you will be given awareness about hypertension and reminders to manage hypertension through WhatsApp. Contact us if you have any confusion or doubts related to hypertension and its management without hesitation.”

**Figure 6. F6:**
[figure not shown]
Participant-specific health messages related to healthy lifestyle and medication. (A) Translation of the messages from the chat page of Intervention PDM 7 (a physician-diagnosed participant with hypertension taking antihypertensive medication): “1) Include vegetables, fruits, and whole grains in the diet; 2) The practice of regular physical activities helps to control hypertension, so, fix a time for exercise in the morning or evening; 3) This is a reminder to take your anti-hypertensive medication on time. Try to have an appointment with your consulting doctor at least once every 4 weeks.” (B) Translation of the messages from the chat page of Intervention CS 3 (hypertension case found during screening): “Measures to control hypertension—practice exercise daily (at least 150 minutes a week), include fruits and vegetables in the diet (take at least 4-5 servings a day), restrict excess salt intake (consume only less than 5 gm), stop using tobacco, and control consuming alcohol” (from the poster) and “It is important to reduce mental stress to control hypertension” (from the message).

Participants in the control group will be advised to continue standard hypertension care and reminded of the follow-up survey 3 months after the baseline survey. To ensure that the participants in the control group also benefit from being part of the study, they will receive the messages and posters after the follow-up survey.

#### Data Collection Tools and Techniques

Prospective participants will be screened using a checklist. Blood pressure will be measured as per the guidelines of the World Health Organization and the American Heart Association [29,30] using an Omron HEM-7113 blood pressure monitor [31,32]. The responses to the questionnaire will be self-reported by the participants. Lifestyle factors (ie, diet, physical activity, and tobacco use) and medication adherence will be assessed before and after the intervention period. Lifestyle factors will be assessed through a series of questions on fruit and vegetable intake, salt consumption, processed food intake, physical activity, tobacco use, and alcohol consumption. Medication adherence will be assessed using the Hill-Bone Medication Adherence Scale and a self-developed questionnaire to assess the reasons for nonadherence to medication [33,34]. The *KoboToolbox* application will be used along with the pen-and-paper approach to collect survey data. Additional physical measurements, such as waist and hip circumference, will be taken using the Seca ergonomic retractable tape at baseline and follow-up [31,32,35]. Both the baseline and follow-up surveys will be conducted at the participants’ homes. Responses to WhatsApp messages will be recorded in a Microsoft Excel spreadsheet throughout the intervention period. All the tools (Table 1) are prepared in English, translated into Malayalam, and back translated into English. Loss to follow-up will be managed through revisits and prescheduled interviews based on the participants’ convenience except in cases of refusal, migration, or death.

**Table 1. T1:** Data collection tools and techniques, along with the operationalization of variables.

Tool or technique and variable	Operationalization	References
Checklist for screening		
Eligibility factors	Age in years; self-reported pregnancy status, disability status, recent surgery, type 1 diabetes mellitus, and life-threatening diseases; access to a smartphone and WhatsApp via a “yes” or “no” question, and if yes, specify whose smartphone they have access to	[4,27,36]
Adapted questionnaires for the baseline survey		
Socioeconomic status	On the basis of the modified Kuppuswamy scale, a score of 26-29 indicates upper socioeconomic class, 16-25 indicates upper-middle socioeconomic class, 11-15 indicates lower-middle socioeconomic class, 5-10 indicates upper-lower socioeconomic class, and <5 indicates lower socioeconomic class	[37]
Sociodemographic characteristics	Self-reported sex, residence, marital status, educational level, occupation, living arrangements, monthly family income, number of children, and household members	[38]
Digital health literacy	Captured using a 6-item Likert-type questionnaire; based on the responses, a higher score denotes a higher digital health literacy	[39]
Intention to use the mHealth^a^ strategy	Captured using a 5-domain questionnaire with 20 items; based on the responses, a higher score denotes a higher intention to use the mHealth strategy for hypertension management	[30]
Physical measurements for screening and the follow-up survey		
Hypertension status	A physician-diagnosed case of hypertension and/or when blood pressure is measured and shows SBP^b^ ≥140 mm Hg and/or DBP^c^ ≥90 mm Hg	[40]
Hypertension emergency	When blood pressure is measured and shows SBP ≥180 mm Hg and/or DBP ≥110 mm Hg	[24]
Physical measurements for the baseline and follow-up surveys		
Waist circumference	Controlled waist circumference ≤90 cm for male individuals and ≤80 cm for female individuals	[35]
Waist-to-hip ratio	Controlled waist-to-hip ratio ≤0.90 for male individuals and ≤0.85 for female individuals	[35]
Adapted questionnaires for the baseline and follow-up surveys		
Awareness of hypertension	A total score will be calculated based on responses to 12 questions; the higher the score, the higher the awareness	[33]
Alcohol consumption and tobacco use	Responses of “yes” or “no”; if yes, then subsequent questions will be asked to assess frequency and pattern of alcohol consumption and the type of tobacco use	[40]
Processed food intake, fruit and vegetable intake, and salt intake	On the basis of the Nova classification system for processed food (based on level of processing) and adherence to the diet	[41,42]
Physical activity	Considered adequate when an individual has at least 150 min per wk of moderate activity or at least 75 min per wk of vigorous activity or an equivalent combination; the leisure-time physical activity will be considered adequate when the individual has at least 300 min per wk	[43]
Medication adherence status and reasons for nonadherence	On the basis of the Hill-Bone Medication Adherence Scale, the higher the total score, the poorer the adherence; in addition, the higher the score, the more reasons for nonadherence to medication	[33,34]
Treatment questionnaire for the baseline survey		
Status of health care service use for diagnosis, treatment, and others	Diagnosis of hypertension and comorbidities, duration of hypertension, frequency of blood pressure monitoring, type of health care facility for service, and status of telemedicine or mHealth service use	[38,40]
Treatment questionnaire for the baseline and follow-up surveys		
Details on antihypertension medication	Medication status, along with frequency and duration of medication; side effects of medication	[38,40]

a mHealth: mobile health.

b SBP: systolic blood pressure.

c DBP: diastolic blood pressure.

#### Validity and Reliability of the Tools and Measurements

The content and face validity of the tools were improved through literature and peer reviews. All the adapted questionnaires used for the study will be tested for internal consistency using Cronbach α values. Physical measurements and blood pressure measurements will be taken by the principal investigator of the study, who is a trained medical graduate with a Bachelor of Ayurvedic Medicine and Surgery and a Master of Public Health and currently pursuing a PhD in Public Health. Standard equipment and specific cutoffs will be used as per standard protocols for blood pressure [30], waist circumference, and waist-to-hip ratio measurement [35]. The electronic blood pressure monitor will be checked for accuracy using a calibrated sphygmomanometer from the health center.

#### Study Outcomes

The primary outcomes are the evaluation of the impact of the WhatsApp-led mHealth strategy on blood pressure measurements and adherence to medication and a healthy lifestyle in adults with hypertension aged between 40 and 59 years.

The secondary outcomes are the estimation of the prevalence and control of hypertension; percentage of participants adhering to antihypertensive medication; and prevalence of tobacco use, alcohol consumption, physical activity, diet patterns (such as frequency of fruit and vegetable consumption and processed food intake), and salt intake, as well as the estimation of digital literacy and the intention to use the mHealth strategy among adults with hypertension aged 40 to 59 years.

#### Statistical Analysis

The survey data collected will be entered into a Microsoft Excel spreadsheet and then exported to SPSS (version 26; IBM Corp) for coding and analysis. Codebooks and frequency tables will be generated to characterize the responses and identify any data entry errors. The missing data will be characterized as missing at random and missing not at random. The data missing at random will be addressed by creating a new variable or recoding an existing variable to account for the missing response. The data missing not at random will be addressed using the last observation carried forward approach (if the missing data were due to loss to follow-up) or regression imputation. Case deletion will be used if there are any missing data observed in multiple outcome variables. The analysis will be conducted adhering to the intention-to-treat approach. Study variables will be developed based on the operationalization plan shown in Table 1.

Descriptive analyses, including frequencies and percentages for categorical variables and means and SDs for continuous variables, will be conducted to understand the sample characteristics. The sociodemographic and health-related characteristics of the intervention and control groups will be compared at baseline. Furthermore, the outcome variables, including medication and lifestyle factors, will be compared between and within the intervention and control groups using baseline and follow-up data.

The comparison of categorical outcomes (medication and lifestyle factors) between and within the intervention and control groups will be conducted using the chi-square test and logistic regression. The regression analysis will be reported as unadjusted odds ratios with 95% CIs. The comparison of continuous outcomes (waist-to-hip ratio, awareness of hypertension, medication adherence score, and duration of physical activity) between the intervention and control groups will be conducted using a 2-tailed independent-sample *t* test (for normally distributed data) and the Mann-Whitney *U* test (for nonnormally distributed data). For comparisons of continuous outcomes within the intervention and control groups, a paired *t* test (for normally distributed data) and a Wilcoxon signed-rank test (for nonnormally distributed data) will be used.

The generalized estimating equations model will be used to assess the effectiveness of the mHealth intervention based on the longitudinal study data (data from the baseline and follow-up surveys). Variables such as time, intervention, time-intervention interaction, and other sociodemographic factors will be considered in the model. The analysis using the generalized estimating equations model will be presented as adjusted odds ratios with 95% CIs. The significance will be considered at a *P* value of less than .05.

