Participants in the intervention group will be advised to follow standard hypertension care. Additionally, participants will be invited to join the intervention through an invitation message and will be listed to receive personalized hypertension management messages via WhatsApp (Figures5  6). The health messages and posters will be shared in the morning at around 6 to 7 AM. Messaging will start within a month following the baseline survey. The intervention will continue from that day for the next 90 days. In the first month (first 30 days), messages will be shared daily; in the second month (middle 30 days), messages will be shared twice a week; and in the third month (last 30 days), messages will be shared once a week (7 days). There will not be a specific day of the week to send messages; days will be calculated from the first day that participants start receiving messages, not from the beginning of a month or a week. The messages will be shared in the participants’ preferred language (English or Malayalam), and their responses will be documented to check for participant engagement. The follow-up survey will be conducted after 3 months at the end of the intervention period. Participant engagement with the intervention will be actively monitored throughout the intervention period. A total of four steps will be followed as part of the audit trail to ensure that the messages are seen by the participants: (1) highlighted tick marks for each message shared with the participants, (2) message viewing status from the message information option on WhatsApp, (3) any response (in the form of a like or emoji) or comment from the participants after receiving the message or poster that was shared with them, and (4) monthly confirmation through phone call or home visit to ensure that the participants are receiving the messages. Any instances of disengagement from the participants will be noted and followed up on (through WhatsApp messaging, home visit, or phone call) by the principal investigator to reinforce the importance of being actively involved in the study and address any concerns.

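### The missing-data rules conflict for anyone who misses the single follow-up survey, and the methods do not fit the mechanisms they are assigned to

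*Protocol article*

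**What the plan says.** All the rules stand in one paragraph of the Statistical Analysis section of the protocol article:

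- MAR: "The data missing at random will be addressed by creating a new variable or recoding an existing variable to account for the missing response".
- MNAR: "using the last observation carried forward approach (if the missing data were due to loss to follow-up) or regression imputation".
- Several outcomes missing: "Case deletion will be used if there are any missing data observed in multiple outcome variables".
- Population: "The analysis will be conducted adhering to the intention-to-treat approach".

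No order of precedence and no exception is given.

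Two other places decide how these rules work in practice. The intervention section provides one post-baseline assessment: "The follow-up survey will be conducted after 3 months at the end of the intervention period". Study Outcomes makes several things primary together: "blood pressure measurements and adherence to medication and a healthy lifestyle in adults with hypertension aged between 40 and 59 years". According to Data Collection Tools and Techniques, losses are to be limited by revisits and prearranged interviews, but refusal, migration and death are accepted as unrecoverable.

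**The concern.** **Conflict.** Blood pressure, medication adherence and lifestyle are all collected at the same follow-up survey. A participant who misses it has no follow-up value for any of them. One rule carries that person's baseline forward and another removes the person. Two analysts following the text could therefore report different populations and different estimates, and one of those populations would not be intention-to-treat.

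**Mismatch.**
- Regression imputation predicts missing values from observed ones and is valid under MAR, yet it is assigned to MNAR data.
- LOCF with one baseline and one follow-up asserts that nothing changed. It is not a model for MNAR.
- Recoding missingness as a category or new variable does not recover a missing outcome, so it is not a valid MAR method if it is applied to outcomes.
- The method depends on a MAR or MNAR label that observed data cannot verify, so the choice rests on the analyst's judgement.

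This is not detail left to an analysis plan. The article states the rules, and as stated they cannot all be followed.

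**Working it through.** **Step 1: which rules reach a participant lost to follow-up.** The number of missing follow-up outcomes is more than one, so the deletion trigger is met. The cause is loss to follow-up, so the LOCF trigger is met if the values are labelled MNAR. If they are labelled MAR, the recoding rule applies instead. One person can thus fall under deletion, LOCF or recoding. Only deletion removes the person from the analysis.

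**Step 2: source of the figures.** From Sample Size: diastolic mean 80.9 (SD 10.9) before and 75.4 (SD 11.5) after, a difference of 5.5 mm Hg; 80% power; 95% confidence; 20% nonresponse; design effect 1.5; 120 per arm. The stated size reproduces:
- SD = sqrt((10.9² + 11.5²)/2) = 11.204
- n = 2 × (11.204 × (1.960 + 0.842)/5.5)² = 65.1, so 66 per arm
- 66 × 1.5 = 99, and 99 × 1.2 = 118.8, so 119 per arm against the stated 120

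The sample size is not in dispute. It supplies the 5.5 and the 20%.

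**Step 3: equal loss.** Assume that 5.5 mm Hg is the true between-arm difference, that loss is equal in both arms, and that it is unrelated to the change a participant would have shown. LOCF difference = 5.5 × (1 − loss).

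| Loss | Analysed after deletion | Analysed under LOCF (assumed zero changes) | LOCF difference, mm Hg |
|---|---|---|---|
| 5% | 228 | 240 (12) | 5.2 |
| 10% | 216 | 240 (24) | 4.95 |
| 20% | 192 | 240 (48) | 4.4 |

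Only the 20% stands in the document, and there it is a nonresponse allowance. Under these assumptions deletion leaves the 5.5 unbiased.

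**Step 4: unequal loss.** Let the control arm fall by c and the intervention arm by c + 5.5, with loss Li (intervention) and Lc (control). LOCF difference = (c + 5.5)(1 − Li) − c(1 − Lc). The values of c, Li and Lc below are assumptions.
- c = 5, Li = 25%, Lc = 15%: 10.5 × 0.75 − 5 × 0.85 = 3.6
- c = 5, Li = 15%, Lc = 25%: 10.5 × 0.85 − 5 × 0.75 = 5.2
- c = 4, Li = 5%, Lc = 20%: 9.5 × 0.95 − 4 × 0.80 = 5.8

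The size of the bias, and in the last case its direction, depends on which arm loses more.

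**The case against.** **Deletion of every lost participant.** A reader might infer that the plan deletes everyone lost to follow-up. The text does not establish that. LOCF is named first and is tied to loss to follow-up. If it is applied first, no missing outcome is left to trigger deletion, and deletion would cover only people who were surveyed but left several outcomes blank. What stands is the missing order.

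**Recoding of outcomes.** The recoding sentence follows codebooks, frequency tables and data-entry checks and does not mention outcomes. A missing category for questionnaire items is a fair reading. The criticism therefore holds only if the rule is used for outcomes, which the text leaves open.

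**Standard errors.** A reader might infer that LOCF makes the standard error 11% too small, from sqrt(96/120) = 0.89. That assumes an unchanged outcome SD. Take change scores with an assumed baseline to follow-up correlation of 0.5, 20% loss, no control change and a 5.5 mm Hg intervention fall:
- Variance of change = 10.9² + 11.5² − 2 × 0.5 × 10.9 × 11.5 = 125.7
- Deletion: SE = sqrt(2 × 125.7/96) = 1.62
- LOCF: arm variances are 0.8 × 125.7 = 100.6, and 100.6 + 0.8 × 0.2 × 5.5² = 105.4; SE = sqrt((100.6 + 105.4)/120) = 1.31

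The ratio is 0.81, and 1.31 is about right for the LOCF estimator itself. The estimate shrinks in step: 4.4/1.31 = 3.36 against 5.5/1.62 = 3.40. The fault is bias, and no claim about the standard error or lost power is made here.

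**Magnitude.** No attrition rate is stated, home revisits are planned, and the 5.5 is a before-after difference from another trial. This objection stands in full, so the figures only illustrate. It cannot be said, however, that LOCF is always conservative: the last case in Step 4 exceeds 5.5.

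**Conclusion.** The point holds as a conflict between stated rules and a mismatch of method to mechanism. LOCF and case deletion both apply to a participant who misses the one follow-up survey, nothing says which prevails, and deletion would contradict the intention-to-treat statement. Regression imputation is assigned to MNAR, LOCF asserts zero change, and the label that chooses between methods cannot be checked.

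If loss were 20% in each arm and unrelated to change, the choice would be between 192 and 240 participants and between 5.5 and 4.4 mm Hg. Under the assumed 25% and 15% losses with a 5 mm Hg control fall, LOCF gives 3.6 or 5.2, depending on which arm loses more.

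The plan should be corrected, but the documents do not show that the result will be seriously distorted. Because no attrition rate is given, this is a should-fix and not a must-fix.

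**What to change.** Replace the paragraph's rules for outcomes with one ordered scheme:

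1. Analyse all enrolled participants in their allocated arm.
2. Name one primary approach for missing follow-up outcomes, under MAR: multiple imputation by arm, using baseline outcome, medication status, urban or rural unit, age and sex, followed by the planned GEE model with estimates pooled across imputations.
3. Delete case deletion, recoding and single regression imputation as rules for outcomes. If recoding is meant for questionnaire items that are not outcomes, say so.
4. Examine MNAR by a delta-adjusted sensitivity analysis over a prespecified range, set separately for blood pressure and for the adherence and lifestyle outcomes.
5. Keep LOCF, if at all, as a labelled sensitivity analysis.
6. Report loss to follow-up by arm, with reasons.

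The cost is analysis-plan wording and a little more analysis work; no new data are needed. The article reports data collection complete in August 2025 and analysis due by April 2026, so the wording should be fixed and dated before outcomes are compared by arm. If that comparison has already begun, the change should be reported as made afterwards.

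### Before-after changes in categorical outcomes within an arm are paired, but the plan tests them with chi-square and unadjusted logistic regression, and it does not rank these tests below the GEE

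*Protocol article*

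**What the plan says.** All of this stands in the protocol article, Statistical Analysis (quantitative phase).

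- Scope: outcome variables "will be compared between and within the intervention and control groups using baseline and follow-up data".
- Categorical outcomes (medication and lifestyle factors): comparisons "between and within the intervention and control groups will be conducted using the chi-square test and logistic regression". One pair of methods serves both the between-arm and the within-arm comparison. "The regression analysis will be reported as unadjusted odds ratios with 95% CIs".
- Continuous outcomes (waist-to-hip ratio, awareness, medication adherence score, activity duration), between arms: a "2-tailed independent-sample *t* test (for normally distributed data) and the Mann-Whitney *U* test (for nonnormally distributed data").
- Continuous outcomes, within arms: "a paired *t* test (for normally distributed data) and a Wilcoxon signed-rank test (for nonnormally distributed data) will be used".
- Effectiveness: "The generalized estimating equations model will be used to assess the effectiveness of the mHealth intervention based on the longitudinal study data". Its terms are time, intervention, their interaction and sociodemographic factors. Results are to be shown as adjusted odds ratios.
- A single threshold, P below .05, is given for the whole section.

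Data Collection Tools and Techniques states that lifestyle factors and medication adherence are measured before and after the intervention, so each participant contributes two linked answers.

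**The concern.** A Pearson chi-square test that sets baseline counts against follow-up counts treats 120 people seen twice as 240 different people. Ordinary logistic regression of the answer on visit does the same. Both ignore the covariance between a person's two answers. If that covariance is positive, as is usual for habits such as tobacco use or taking tablets, the standard error of the change is overstated. This is not just an article leaving out detail. A method is named, and the paired t and signed-rank tests nearby show that pairing was recognised for continuous outcomes and not carried over to categorical ones.

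Adherence to medication and a healthy lifestyle is among the primary outcomes (Study Outcomes), so the affected comparisons are not peripheral. A real change within an arm may be reported as non-significant, with an interval that is too wide.

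There is also a question of hierarchy. Within-arm tests, unadjusted between-arm tests and the GEE all use the same threshold, and nothing says which one carries the claim. A significant change in one arm beside a non-significant change in the other is easily read as an effect, although it compares nothing between arms.

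**Working it through.** **Inputs.** From the plan: 120 per arm, 20% nonresponse, significance at .05. The documents give no proportions and no within-person correlation for any categorical outcome. Those used below are assumptions, shown as a range.

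**The plan's own figure.** The sample size rests on diastolic pressure: (10.9² + 11.5²) × (1.960 + 0.842)² / 5.5² = 65.1, so 66 per arm. Then 66 × 1.5 = 99, and 99 × 1.2 = 118.8, so 119 per arm, which agrees with the stated 120. This point leaves it unchanged.

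**Type I error.** Let the proportion be p at both visits, with n pairs and within-person correlation ρ.
- Standard error assumed by the independent test: √[2p(1−p)/n].
- True standard error of the change: √[2p(1−p)(1−ρ)/n].
- The test therefore rejects when |Z| exceeds 1.96/√(1−ρ). At ρ = 0.5 this is 2.77, a true level of 0.56%. At ρ = 0.3 and 0.7 the formula gives 1.9% and 0.03%.

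**Power, worked once by formula.** Take n = 120, 50% to 65%, ρ = 0.5.
- Independent test: √(2 × 0.575 × 0.425 / 120) = 0.0638, so the change must exceed 1.96 × 0.0638 = 0.125.
- True standard error: √[(0.25 + 0.2275 − 2 × 0.5 × √(0.25 × 0.2275)) / 120] = 0.0446.
- Power = P(Z > (0.125 − 0.150)/0.0446) = P(Z > −0.56) = 71%.

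**Simulation** (40,000 samples per setting, nominal 5%):

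| Pairs | ρ | True level at 50%/50%: chi-square | McNemar | Power for 50% to 65%: chi-square | McNemar |
|---|---|---|---|---|---|
| 120 | 0 | 4.6% | 4.9% | 66% | 65% |
| 120 | 0.3 | 1.7% | 4.9% | 68% | 80% |
| 120 | 0.5 | 0.5% | 4.9% | 71% | 93% |
| 120 | 0.7 | 0.04% | 5.0% | 76% | >99% |
| 96 | 0.3 | 2.0% | 5.1% | 57% | 71% |
| 96 | 0.5 | 0.5% | 5.4% | 58% | 86% |
| 96 | 0.7 | 0.04% | 4.8% | 59% | 99% |

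The 96 pairs are 120 × 0.8, that is, the arm after 20% loss.

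**Illustration** (assumed counts). Of 120 people, 60 are adherent at baseline and 74 at follow-up; 48 are adherent at both visits, 12 lose adherence and 26 gain it.
- Independent chi-square: 3.31, p = 0.069.
- McNemar: (26 − 12)²/(26 + 12) = 196/38 = 5.16, p = 0.023 (exact p = 0.034).
- Odds ratio: (74/46)/(60/60) = 1.61. Ignoring pairing, the standard error of its logarithm is √(1/74 + 1/46 + 1/60 + 1/60) = 0.262, giving a 95% interval of 0.96 to 2.69.
- Allowing for pairing: the covariance of the two answers is 48/120 − 0.500 × 0.617 = 0.0917. The squared standard error falls by 2 × (0.0917/120)/(0.250 × 0.2364) = 0.0259, from 0.0686 to 0.0427. The standard error becomes 0.207 and the interval 1.07 to 2.41.
- A chi-square on the baseline-by-follow-up cross-table gives 17.06, p < 0.001. That tests whether the two visits are associated, not whether adherence changed.

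**Within-arm significance is not a comparison of arms.** Suppose both arms truly change by the same amount and each within-arm test has power π. Exactly one arm is then significant with probability 2π(1−π): 2 × 0.8 × 0.2 = 32% at 80% power, and 50% at 50% power.

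**The case against.** The strongest reply is that the plan already names a sound effectiveness analysis. The GEE uses both waves, accounts for repeated measures, and contrasts the arms through the time-by-intervention term. The chi-square error therefore falls on supporting comparisons. It is also conservative: it costs power and precision but does not create false positives. Its size depends on a correlation that nobody has stated. For 96 pairs and a change from 40% to 52%, power is 37% against 46% at correlation 0.2, and 36% against 51% at 0.3, a smaller loss than at 0.5 (34% against 67%). The authors may also have meant McNemar's chi-square.

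Most of this stands and limits the point. What remains is that the text assigns an unpaired method to paired data and names no paired alternative. It also does not rank the GEE above the other tests, and it shows the GEE only as odds ratios. For continuous outcomes the only between-arm comparison spelled out on a suitable scale is therefore the unadjusted two-sample test.

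Three stronger readings are tempting and not supported:

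- A reader might infer that the between-arm tests use follow-up values only. The section says that baseline and follow-up data are used and does not fix whether values or changes are compared.
- A reader might infer from the Table 1 heading "Physical measurements for screening and the follow-up survey", which covers the blood pressure classification, that the entry reading doubles as baseline and that regression to the mean will pass for benefit. The Results section says that the baseline survey covers blood pressure before the intervention, so this is not established. Blood pressure is also in neither of the outcome lists given for the simple tests. A fall common to both arms cancels in the GEE interaction.
- A reader might infer that baseline imbalance goes uncorrected throughout. That describes the simple tests, not the GEE.

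**Conclusion.** The point holds in a limited form. For within-arm change in categorical medication and lifestyle outcomes, the stated methods ignore pairing. For any positive within-person correlation the P values are too large and the odds-ratio intervals too wide. At assumed correlations of 0.3 to 0.7 with 120 pairs, the true level is about 1.7% down to 0.04%. Power for an assumed change from 50% to 65% falls short of McNemar's by about 12 to 24 percentage points (80 − 68 = 12; 93 − 71 = 22; just under 100 against 76). At zero correlation there is no difference. The direction is general; the sizes depend on the assumed correlations and proportions.

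The GEE interaction is not affected, so it would be wrong to conclude that the trial's effectiveness estimate is invalid. What needs settling around the GEE is its precedence over the simple tests and the scale for continuous outcomes.

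**What to change.** 1. For within-arm change in categorical outcomes, replace chi-square and ordinary logistic regression with McNemar's test, or with GEE or conditional logistic regression where an odds ratio is wanted. State which odds ratio is reported, because the two models estimate different ones: in the illustration above the marginal value is 1.61 and the conditional value is 26/12 = 2.17. Keep chi-square for the between-arm comparison.
2. Label all within-arm tests and the unadjusted between-arm tests as descriptive, and say that no effectiveness claim will rest on them.
3. State that effectiveness is judged on the time-by-intervention term of the GEE. Use an identity link, reported as mean differences with 95% confidence intervals, for continuous outcomes, and odds ratios for binary ones.

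The cost is analysis wording and a different menu choice in the software. No new data are needed and the sample size is unchanged. The article expects analysis to finish by April 2026. If results have already been examined, the change should be dated and reported as made after data collection.
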